**Discussion:**

Dysphagia is a common complication of stroke. There is lack of high-quality evidence for the efficacy of BTX in treating neurogenic CPD. This study will clarify whether BTX injection into the cricopharyngeal muscle can be effective and safe for patients with stroke and CPD.

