## Methods and design

### Objective

To explore the efficacy and safety of BTX for treatment of neurogenic cricopharyngeal achalasia, with BTX injection guided by ultrasound, catheter balloon, and electromyography, a novel precise positioning method.

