### Allocation and randomization

The late group will initially act as the control group for the early group but will receive BTX treatment later if no improvement of FOIS is achieved. Qualified subjects will be randomized (1:1) in a double-blind fashion to the early group or late group (placebo-control). The randomization sequence was generated by a statistician using the Statistical Package for Social Sciences. A number from 1 to 44 was randomly generated and the random envelopes were generated according to the randomization sequence. The principle investigator (PI) is enrolling patients. A nurse who does not join in the assessment and treatment of the participants will assign participants to their allocation according to the random envelopes. Throughout the double-blind phase of the study, patients and investigators will not be informed of the treatment-group assignment. The BOTOX and placebo will be provided in identical syringes, allowing double-blinded administration. One nurse will be responsible for the dilution of BOTOX and placebo. Unblinding is permissible if there are any adverse events, or participants request the termination of the trial. When unblinding becomes necessary, the principal investigator (PI) will report the reason for the unblinding of patients and the associated adverse event (if exist) to the Data Monitoring Committee, who will jointly decide whether to unblind or not. Once unblinded, the participating investigators, the patient and his/her family will be informed of the patient’s allocation by the nurse who know the patient allocation. All interventions, examination results, adverse events, and reasons for unblinding will be documented.

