### Sample size estimates

To detect significant differences between groups using an independent sample *t* test, a sample size of 44 patients is needed, assuming a spontaneous recovery mean ± SD in the late group of 2.6 ± 1.1 [29, 30], and a recovery mean ± SD of 4 ± 1.8 in the early group, as determined by our pilot study. These estimates assume a type I error of 0.05, a power of 0.80, and an estimated 10% rate of loss to follow-up.

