### Statistical analyses

The statistical analysis will be performed using the Statistical Package for Social Sciences (SPSS) version 23.0 for Windows by a statistician who is not involved in the study. A chi-square test will be used to compare the expulsion rate between the early and late groups. If the expulsion rate of the two groups is not statistically significant (*p* > 0.05), compliance of the groups will be considered similar. On the contrary, it is considered that the compliance of the two groups of patients is inconsistent, and it is necessary to re-recruit research cases, which will be assessed by the Data Monitoring Committee. Normally distributed data will be presented as the mean ± standard deviation. Categorical data will be presented as the frequency and proportions. Assumptions of normality will be tested with the Kolmogorov-Smirnov test. The parametric data will be analyzed by the independent sample *t* test, while the non-parametric data will be analyzed by the rank sum test. The *p* values ≤ 0.05 will be considered statistically significant. A comparison between two groups will be used to assess whether the efficacy (represented by FOIS, UES residual pressure, UES resting pressure, duration of UES relaxation, etc.) is different. A chi-square test will be used to compare the differences in the proportion of patients with improved swallowing function (assessed by FOIS) between the groups. Improvement prior to and post treatment in both groups will be assessed. Efficacy evaluation indicators (FOIS, UES residual pressure, UES resting pressure, duration of UES relaxation, etc.) will be compared two weeks after the first and second injections to assess improvement in the groups. A logistic regression method will be used to establish a probability model of BTX efficacy and influencing factors. The effect of each influencing factor on BTX efficacy (OR and 95% confidence interval) will be quantitatively analyzed to determine the interpretable accuracy and reliability of the coefficient *R*^2^ evaluation of the established efficacy and influencing factors model, with the FOIS score of the BTX group will be defined into effective and non-effective, a two-category variable *Y* (FOIS ≥ 3, *Y* = 1; FOIS<3, *Y* = 0). Patients’ age, gender, stroke lesion location, UES residual pressure, UES resting pressure, duration of UES relaxation, velopharyngeal peak pressure and hypopharyngeal peak pressure, UES opening, pharyngeal construction ratio, residue of bolus in the epiglottis valley or piriform sinus, penetration, and aspiration will be used as influencing factors of variable Xi (*i* = 1, 2, …11). A chi-square test will be used to compare the incidence of adverse events between the groups. An interim analysis will be performed after inclusion of the first 22 patients by a statistician who is not involved in this research. The data collection of the study will be assessed and confirmed by the Data Monitoring Committee, which can make decision to stop the research when it is harmful or futile.

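### The only between-arm safety analysis is a chi-square test with 22 patients per arm, so a non-significant result could not support a statement that BTX is safe

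*Protocol article*

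**What the plan says.** The Objective section of the protocol article reads "To explore the efficacy and safety of BTX for treatment of neurogenic cricopharyngeal achalasia", and the Discussion part of the abstract says "This study will clarify whether BTX injection into the cricopharyngeal muscle can be effective and safe for patients with stroke and CPD".

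Under Statistical analyses, the between-arm comparison of harms is one sentence: "A chi-square test will be used to compare the incidence of adverse events between the groups". The general rule in that section is that p "values ≤ 0.05 will be considered statistically significant". No confidence interval or excess-risk criterion is attached to adverse events, and no time window is given for the comparison.

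The Sample size estimates section rests on FOIS means. It opens "To detect significant differences between groups using an independent sample" t test and concludes that "a sample size of 44 patients is needed". Randomization is 1:1, so there are 22 per arm.

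The same Statistical analyses paragraph handles another chi-square comparison, that of expulsion rates, by a rule: if p > 0.05, "compliance of the groups will be considered similar".

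Other safety provisions are stated. Categorical data are shown as counts and proportions. Severity, causality, seriousness and outcome are assessed for each event. The Data Monitoring Committee is told within 3 days and may stop the trial for harm.

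**The concern.** A difference test can give evidence of harm. Failing to reject says little about the absence of harm unless the test had good power against an excess that matters. This trial was sized for a mean difference in FOIS, so its power for adverse events is whatever 22 per arm happens to give.

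The events that the article itself lists are hoarseness, gastroesophageal reflux, local bleeding and aspiration pneumonia. If the main comparative result is a p value above 0.05, the report has no figure for how large an excess the data still allow. That figure is what a reader of a trial with a safety objective needs.

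**Working it through.** **1. The plan's own figure.** Inputs from Sample size estimates: means 2.6 and 4, SDs 1.1 and 1.8, type I error 0.05, power 0.80, loss 10%. Pooled SD = √((1.1² + 1.8²)/2) = √2.225 = 1.49, and the difference is 1.4. A two-sided t test (noncentral t) needs 19 per arm (power 0.804). Then 19/0.9 = 21.1, rounded up to 22 per arm, or 44 in total. The stated 44 reproduces, and it comes from FOIS only. After 10% loss, 44 × 0.9 = 39.6, about 20 per arm.

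**2. Power of the stated safety test.** All adverse event rates are assumptions. For each pair of rates I summed the product of the two binomial probabilities over every table with p ≤ 0.05 and more events on BTX. The test is the Pearson chi-square without continuity correction, X² = N(ad − bc)² / (product of the four margins).

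| Placebo v BTX rate | Excess (points) | 22 per arm | 20 per arm |
|---|---|---|---|
| 5% v 15% | 10 | 18% | 15% |
| 5% v 20% | 15 | 33% | 29% |
| 5% v 25% | 20 | 49% | 44% |
| 10% v 20% | 10 | 15% | 14% |
| 10% v 25% | 15 | 26% | 24% |
| 10% v 30% | 20 | 39% | 36% |
| 20% v 30% | 10 | 11% | 11% |
| 20% v 40% | 20 | 30% | 29% |
| 5% v 30% | 25 | 64% | 59% |
| 10% v 35% | 25 | 53% | 49% |
| 10% v 40% | 30 | 67% | 62% |
| 0% v 20% | 20 | 67% | 59% |

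For an excess of 10 to 20 points at placebo rates of 5% to 20%, every entry is below one half. Against 5% on placebo, 80% power at 22 per arm needs about 37% on BTX.

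**3. What a non-significant table still allows.** Take 5/22 on BTX and 1/22 on placebo.
- X² = 44 × (5×21 − 1×17)² / (22×22×6×38) = 340,736/110,352 = 3.09, so p = 0.079.
- The observed difference is 4/22 = 18.2 points.
- The Wilson 95% limits are 10.1% to 43.4% for 5/22 and 0.8% to 21.8% for 1/22.
- Newcombe lower limit: 0.182 − √((0.227 − 0.101)² + (0.218 − 0.045)²) = −0.03.
- Newcombe upper limit: 0.182 + √((0.434 − 0.227)² + (0.045 − 0.008)²) = +0.39.

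The result is not significant, yet it is compatible with an excess of up to 39 points.

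**4. No events at all.** With 0/22 on BTX, the exact two-sided 95% upper limit for the BTX rate is 1 − 0.025^(1/22) = 0.154, about 15%.

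**The case against.** **The article has no rule that p > 0.05 means safe.** This is correct. A reader might infer one, because the same paragraph applies that logic to expulsion rates, but the rule is written for expulsion only. The abstract also says that the trial will clarify whether BTX can be safe, not that it is safe, and the objective is to explore. The point is therefore about what the stated analysis can support, not about a false claim already made.

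**The test is not the whole of the safety assessment.** This also stands. Counts and proportions, per-event causality and severity, and independent committee review with power to stop for harm are all stated. None of them gives an estimate of excess risk with its uncertainty.

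**Large excesses would be found.** This is partly right. A reader might infer that any large harm would usually be missed, and the table contradicts that: 5% v 30%, 10% v 40% and 0% v 20% are each detected in about two thirds of trials at 22 per arm. The low power concerns excesses up to about 20 points at placebo rates of 5% to 20%.

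**Small trials are rarely powered for harms, and an unseen analysis plan may hold the reporting detail.** Both are fair. The point does not ask for more patients. It concerns a method that the article does fix, set against an objective that it also states.

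**Should the test be Fisher's instead?** With fewer than 10 events in total, expected counts fall below 5, and the two tests can disagree: 4/22 v 0/22 gives Pearson p = 0.036 and Fisher p = 0.108. Yet under equal rates the uncorrected Pearson test rejects in at most about 5.3% of trials at these sizes. Fisher's test would lower the chance of detecting harm further (5% v 20%: from 33% to 20%). A change of test is not part of this point.

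**Conclusion.** The point holds in a limited form and is a cheap improvement. Safety is a co-stated objective, and the only between-arm safety analysis stated is a significance test in a trial sized for FOIS. With 22 per arm, an excess of 10 to 20 points is detected in 18% to 49% of trials at a 5% placebo rate, 15% to 39% at 10%, and 11% to 30% at 20%. A non-significant result therefore cannot by itself support a statement that BTX is safe.

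This rests on assumed event rates, an uncorrected two-sided chi-square test, and complete follow-up of 22 per arm; 20 per arm gives slightly lower figures. It does not show that the investigators will misread the test, that harms go unmonitored, or that the test is invalid.

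**What to change.** Replace the adverse event sentence in Statistical analyses with text along these lines:

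*Adverse event incidence during the placebo-controlled first two weeks will be reported by arm, with the risk difference (BTX minus placebo) and its 95% confidence interval (Newcombe). Any p value is descriptive. A non-significant difference will not be taken as evidence of safety; the safety statement will quote the upper confidence limit of the excess risk.*

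The window matters because late-group patients with FOIS below 3 can receive BTX at two weeks. Pooling later events by randomized arm would blur the contrast. Rewording the abstract is optional.

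The cost is two or three sentences, with no extra patients or data. The downside is a more cautious safety statement.

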**Methods:**

BECURE is a single-center randomized, placebo controlled, double-blinded, superiority clinical trial. To detect a significant difference between the 2 groups, a sample size of 44 patients is estimated. The intervention is BTX versus placebo, with 1:1 randomization. The randomization sequence from 1 to 44 was generated using the Statistical Package for Social Sciences. The study is divided into two phases. In the first phase, patients will be injected with BTX or the placebo. In the second phase, patients who received a placebo injection and those who did not respond to the first BTX injection will receive an injection of BTX. The primary outcome is the score of the Functional Oral Intake Scale (FOIS). The secondary outcomes are as follows: upper esophageal sphincter (UES) residual pressure, UES resting pressure, duration of UES relaxation, velopharyngeal and laryngopharyngeal peak pressure, UES opening, pharyngeal construction ratio, residue of bolus in the epiglottis valley or piriform sinus, and penetration and aspiration.

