### Definitions

Early group: patients receiving botulinum toxin type A (BOTOX) injection immediately after randomization.

Late group: patients receiving placebo injection immediately after randomization and receive BOTOX injection 2 weeks after randomization if the FOIS score < 3.

Retreat group: patients within the “early group” with a score < 3 of FOIS 2 weeks after BOTOX injection and will receive another BOTOX injection.

Figure 1 is a graphical representation of the study design.

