### Participant timeline

The total duration of participation in the study will be 4 weeks. Figure 2 is a schedule of enrollment, interventions, and assessments for all study patients.

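### The adverse event comparison is not limited to the two weeks in which the late group is a placebo control, so the safety contrast can shrink toward zero

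*Protocol article*

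**What the plan says.** Safety stands beside efficacy in the Objective section. The Statistical analyses section provides one between-group safety analysis: "A chi-square test will be used to compare the incidence of adverse events between the groups". It attaches no observation window, study phase or exposure rule. The same paragraph does give time points for the efficacy indicators, which "will be compared two weeks after the first and second injections to assess improvement in the groups"; its list of those indicators does not name adverse events.

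Participant timeline: "The total duration of participation in the study will be 4 weeks".

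The late group's exposure changes during those weeks, and the article describes the change in three ways:

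- Definitions: "patients receiving placebo injection immediately after randomization", who then "receive BOTOX injection 2 weeks after randomization if the FOIS score < 3".
- Allocation and randomization makes the change depend on response: "The late group will initially act as the control group for the early group but will receive BTX treatment later if no improvement of FOIS".
- Abstract, Methods: "patients who received a placebo injection and those who did not respond to the first BTX injection will receive an injection of BTX", with no condition on the placebo patients.

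The early group can also be injected again. The retreat group is defined as "patients within the “early group” with a score < 3 of FOIS 2 weeks after BOTOX injection and will receive another BOTOX injection".

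The Adverse events section has the onset date of each event recorded.

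**The concern.** A randomised comparison of BTX with placebo exists only until the second injection. After that, late-group patients may have had placebo and then BTX, and early-group patients one or two BTX injections. A count by randomised group over the whole of participation no longer compares BTX with placebo. An event caused by BTX in a late-group patient in week 3 would be charged to the placebo arm.

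The distortion has a predictable direction: it pulls the difference toward zero and so makes BTX look closer to placebo on safety than it is. Because safety is a stated objective, this affects a main conclusion of the trial. A phase-two comparison of the randomised groups would not help either, since it has no pure placebo arm.

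**Working it through.** **The plan's own figures.** The article states no figure for the adverse event comparison. The only related figure is the total of 44, sized on FOIS. It reproduces: difference 4 − 2.6 = 1.4; SD = √((1.1² + 1.8²)/2) = 1.492; two-sided 5% t test with 80% power needs 19 per arm; 19/0.90 = 21.1, rounded up to 22 per arm. This point does not affect it.

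**Shares injected at week 2.** These are a normal approximation to the FOIS means and SDs in Sample size estimates, with the rule FOIS below 3 read as a cut at 3 or, with continuity correction, at 2.5.

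- Late group (2.6 ± 1.1): Φ((2.5 − 2.6)/1.1) = 46%; Φ((3 − 2.6)/1.1) = 64%.
- Early group (4 ± 1.8): Φ((2.5 − 4)/1.8) = 20%; Φ((3 − 4)/1.8) = 29%.

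**Assumed event risks.** Let p₁ be the risk of an event in a two-week period that starts with BTX and p₀ the risk in any other two-week period. Both are assumptions. They apply to both arms in both periods, independently of FOIS. Let c be the share of the late group injected with BTX at week 2 and r the share of the early group retreated.

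- Early, 4 weeks = 1 − (1 − p₁)(1 − [r·p₁ + (1 − r)·p₀])
- Late, 4 weeks = 1 − (1 − p₀)(1 − [c·p₁ + (1 − c)·p₀])

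Worked case, p₁ = 20%, p₀ = 5%, c = 0.46, r = 0.20:

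- Early: second-period risk 0.20 × 0.20 + 0.80 × 0.05 = 0.080; total 1 − 0.80 × 0.920 = 26.4%.
- Late: second-period risk 0.46 × 0.20 + 0.54 × 0.05 = 0.119; total 1 − 0.95 × 0.881 = 16.3%.
- Difference 10.1 points, against 15 points in the first two weeks.

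| Count | Early vs late, 20%/5% | Difference | Early vs late, 30%/10% | Difference |
|---|---|---|---|---|
| First 2 weeks only | 20.0 vs 5.0 | 15.0 | 30.0 vs 10.0 | 20.0 |
| 4 weeks, late 46%, early 20% | 26.4 vs 16.3 | 10.1 | 39.8 vs 27.3 | 12.5 |
| 4 weeks, late 64%, early 29% | 27.5 vs 18.9 | 8.6 | 41.1 vs 30.5 | 10.5 |
| 4 weeks, all late, early 0% | 24.0 vs 24.0 | 0.0 | 37.0 vs 37.0 | 0.0 |
| 4 weeks, all late, early 29% | 27.5 vs 24.0 | 3.5 | 41.1 vs 37.0 | 4.1 |

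**A second model.** Take a background risk of 5% per two weeks and an added risk of 10% to 40% per BTX injection, with the same shares. A 4-week count then keeps 51% to 68% of the two-week difference under conditional crossover, and 0% to 25% if all placebo patients cross over. The direction and rough size agree.

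**The case against.** The strongest reply is that the article never says the comparison covers 4 weeks. That figure is the length of participation, not an analysis rule. The trial is described in two phases, the late group is a control only at first, efficacy is read after each injection, and onset and causality are recorded for each event. A statistician could well analyse adverse events by phase, and an analysis plan that is not shown may say so.

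This stands as far as it goes: pooling over 4 weeks is one reading of unrestricted wording, and the dilution is conditional on it. It does not remove the point. The paragraph fixes the test and the contrast for safety and gives time points for efficacy but none for adverse events. In a design where the control arm changes treatment midway, the contrast so fixed is ill-defined.

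Stronger readings are tempting, but the documents do not support them:

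- **That every placebo patient receives BTX at week 2.** Only the abstract reads that way; Definitions and Allocation and randomization both set a condition.
- **That the difference reverses.** With full crossover this appears only if the late arm is given second-period risk and the early arm none: 1 − 0.95 × 0.80 = 24% against 20%, or −4 points. Early patients also have a second period, and some are retreated. With risk in both arms, the difference is zero or slightly positive.
- **That a non-significant chi-square will be taken as proof of safety.** The article does not say so. It also provides for assessment of severity, causality and seriousness, and for Data Monitoring Committee oversight.

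The Treatment or intervention section has treatment discontinued after listed adverse events, which could reduce second injections. In the model above this matters little for per-patient incidence: a patient with a first-period event is already counted, and the second-period term applies only to those still event-free.

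**Conclusion.** The point holds as a defect in how the safety comparison is specified, not as an established bias. If events are counted by randomised group over participation, the contrast moves toward zero. Under the assumed 20% and 5% risks, 15 points become about 9 to 10 with conditional crossover and about 0 to 4 with full crossover. These sizes rest on assumed event rates, a normal approximation to FOIS for the shares injected, and independence between events and FOIS response. The direction depends only on BTX carrying added risk and on more late-group than early-group patients being injected at week 2. It is worth correcting because safety is a stated objective and the remedy is simple.

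**What to change.** In Statistical analyses, restrict the randomised adverse event comparison to events with onset from the first injection to the week-2 assessment and before any second injection. Report it as a risk difference between early and late groups with a 95% CI. Tabulate later events separately by BTX exposure actually received: first BTX in the late group and second BTX in the retreat group.

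Reconcile the Abstract, Definitions, and Allocation and randomization on who receives BTX in phase two. Besides the unconditional wording in the abstract, a patient who improves but stays below FOIS 3 is injected under Definitions and not under Allocation and randomization.

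The cost is a few sentences; onset dates are already collected, and no new data, visits or patients are needed. The downside is that phase-two events leave the randomised test and are reported descriptively.

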
### Adverse events

Adverse events and unintended effects during the treatment will be reported directly to the sponsor. The investigator will also assess the severity, causality, and seriousness of the adverse events and will inform the Data Monitoring Committee within 3 days of the initial observation of the event. The onset date, manifestations, severity, duration, action taken, and outcome for each adverse event will be recorded. Patients who suffer harm from trial will be cared for and financial compensation will be provided by our department.

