### Exclusion criteria

Patients will be excluded from study participation if any of the following apply:
Suffer from other neurogenic dysphagia or a condition that can cause dysphagia (for example, Parkinson’s disease).Have a non-neurogenic disease (e.g., cancer).Have a neuromuscular disorder (e.g., myasthenia gravis or motor neuron disease).Have psychopathy.Unable to cooperate with examination and treatment.Have infections or cuts at injection site.Allergic to botulinum toxin.Have coagulation dysfunction.Receive or have received anesthetics or any medicine that affects neuromuscular junctions within 1 month prior to participation.Participating in another study that could influence the results of BTX injection on the cricopharyngeal muscle.

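### The adverse-event window is loosely worded, and patients given BTX at week 2 are observed for 14 days after their last injection, against 28 days for early-group patients not re-injected

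*Protocol article*

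**What the plan says.** The Adverse events section states: "Adverse events and unintended effects during the treatment will be reported directly to the sponsor". It does not define that period or say when collection ends. It adds: "The onset date, manifestations, severity, duration, action taken, and outcome for each adverse event will be recorded".

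The section on treatment describes an injection. It lists events such as hoarseness and aspiration pneumonia as arising after administration, and it keeps participants in hospital throughout the study.

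The Participant timeline states: "The total duration of participation in the study will be 4 weeks". Under Definitions, late-group patients "receive BOTOX injection 2 weeks after randomization if the FOIS score < 3", and the retreat group consists of early-group patients "with a score < 3 of FOIS 2 weeks after BOTOX injection and will receive another BOTOX injection". The abstract words the second phase differently: "patients who received a placebo injection and those who did not respond to the first BTX injection will receive an injection of BTX". In Statistical analyses, the efficacy measures "will be compared two weeks after the first and second injections to assess improvement in the groups", and adverse-event incidence is compared between the groups by a chi-square test with no period given.

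Safety is part of the stated objective. The Discussion lists relatively short follow-up as a limitation.

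**The concern.** Two things do not sit well together. First, the reporting period is tied to treatment, which is a procedure on one or two days, while the harms named elsewhere in the article come afterwards. Second, even on the generous reading (the whole participation period), the time at risk after BTX depends on when the last injection was given. A patient injected only at baseline contributes 28 days; a patient injected at week 2 contributes 14.

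At stake is what the trial can say about safety. A pooled adverse-event proportion would mix patients with different observation times after BTX. A between-group comparison over weeks 0 to 4 would also no longer be BTX against placebo, because by then part or all of the late group has had BTX. In the patients injected at week 2, an event arising after day 14 would fall outside the observation period.

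**Working it through.** **Observation time after the last BTX injection**

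- Participation: 4 weeks = 28 days (Participant timeline).
- Second-phase injection: week 2 = day 14 (Definitions).
- Injected at week 2: 28 − 14 = 14 days.
- Early group, not re-injected: 28 − 0 = 28 days.
- Retreated patients: 28 days from their first BTX injection and 14 from their second.

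The assessment schedule figure is not shown, so a later contact cannot be strictly excluded. The Trial status section makes one unlikely: recruitment ends 1 June 2021 and final follow-up 30 June 2021, and 1 June plus 28 days is 29 June.

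**The plan's own figure**

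The patient counts below use the sample-size means and SDs, so I first checked that these reproduce the stated total of 44.

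- Difference: 4 − 2.6 = 1.4. SD: √((1.1² + 1.8²)/2) = 1.492. Standardised difference: 0.939.
- Two-sample t test, two-sided alpha 0.05 (sidedness is my assumption), power 0.80: 18.83, so 19 per arm.
- 19/0.90 = 21.1, so 22 per arm and 44 in total. This agrees.

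**How many patients have only 14 days**

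I assume that the sample-size means apply at week 2, that FOIS is roughly normal, and that nobody is lost. FOIS is an integer scale, so a score below 3 is taken with the cut at 2.5 and at 3.

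| | Cut 2.5 | Cut 3 |
|---|---|---|
| Late: 22 × Φ((cut − 2.6)/1.1) | 22 × 0.464 = 10.2 | 22 × 0.642 = 14.1 |
| Early: 22 × Φ((cut − 4)/1.8) | 22 × 0.202 = 4.5 | 22 × 0.289 = 6.4 |
| Total of 44 | 14.7 (33%) | 20.5 (47%) |
| Ever given BTX (22 + late) | 32.2 | 36.1 |
| Share of those with 14 days only | 46% | 57% |

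Sensitivity:

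- If every placebo patient receives BTX, as the abstract words it, the total is 22 + 4.5 to 22 + 6.4, or about 26 to 28 of 44 (26.45/44 = 60% to 28.36/44 = 64%).
- If early-group non-response is taken from the 43% to 100% success range cited in the Background, retreated patients number 22 × 0 = 0 to 22 × 0.57 = 12.5. The total under the Definitions section is then 10.2 + 0 to 14.1 + 12.5, or about 10 to 27 of 44 (23% to 61%).

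These counts are patients with the shorter window, not missed harms. The documents give no figure from which missed harms could be calculated.

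**The case against.** A reader might infer that collection stops when the needle is withdrawn. The text does not support that. The sentence carries no word of restriction, every event is to be recorded with its duration and outcome, patients stay in hospital throughout, and Data collection and management has adverse events checked and also recorded for dropouts. The 4-week stay is clearly what is meant; what is left is loose wording.

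A reader might also set the 14 days against the exclusion of patients who received "any medicine that affects neuromuscular junctions within 1 month prior to participation" and call that month the protocol's own safety window. It is a general entry exclusion. The protocol does not present it as how long BTX acts or when harm appears, so it is at most an indirect benchmark and there is no contradiction with the 4-week participation.

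Nor can one say that late harm goes unseen or that incidence is understated, because no passage gives the timing of BTX adverse events. It would also mislead to say that the most heavily exposed patients are followed least: on the base-case figures 10 to 14 of the 15 to 20 are late-group patients with one BTX injection, and the retreated have 28 days from their first.

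Three further points stand. The first two weeks are placebo-controlled with equal observation in both arms, so that comparison is not harmed, and anything added later is descriptive. The short follow-up is openly acknowledged. The objective and abstract state aims, not an unlimited claim of safety.

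What the objection does not remove is the 14-versus-28-day difference. The stated limitation does not disclose it, and nothing in the article says that events will be analysed by time since injection.

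**Conclusion.** The point holds as a modest, inexpensive improvement, not as a flaw in the randomised comparison. The date arithmetic is firm, subject to the unseen schedule figure. The number affected is approximate: about 15 to 20 of 44 under the Definitions section, 26 to 28 under the abstract, and 10 to 27 if early-group response is taken from the cited success range. These rest on a normal approximation to an ordinal scale and on reading the sample-size means as week-2 values. Even the lowest figure is 23% of the trial. Events after day 14 would not be observed in these patients; how many there would be is unknown.

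**What to change.** 1. In the Adverse events section, replace the reference to treatment with a defined period: from the first injection to a common minimum time after each patient's last injection. Matching the 28 days of early-group patients not re-injected would place the end at day 14 + 28 = day 42 for patients injected at week 2.
2. For patients injected at week 2 and still to be followed, add one adverse-event-only contact by telephone or chart, with no extra manometry, fluoroscopy or endoscopy.
3. Report adverse events by time since last BTX. Present the placebo-controlled weeks 0 to 2 separately from the period after the second injection, and apply the between-group test to the former.
4. If the 4-week limit is kept, confine the safety conclusion to 14 days after injection.
5. Reconcile the abstract and the Definitions section on who receives second-phase BTX, since the number of contacts depends on it.

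Cost: one brief contact per affected patient, and final follow-up about two weeks later (30 June 2021 to about mid-July 2021). The 10 participants who had completed the intervention at manuscript submission would keep the shorter window and should be identified in the report. Events found by telephone after discharge are ascertained differently from those found in hospital, which is a further reason to tabulate the periods separately.
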